### Sample size determination with statistical power calculation

Data will be obtained from 712 families at baseline, with 2 children and up to 2 parents per family (given divorce rates, 1.66 parents per family are estimated). Stratification will be used to over-select female service members and high-risk families such that 456 families will have female military parents and 356 families will be high risk. Power is calculated for three types of analytic samples:

A baseline/cross-sectional analysis sample of 712 families and 1,424 children (2 per family), and 1,182 parents (1.66 per family);A panel analysis sample composed of families who participate at both waves of the study. Based on experience and other military studies [44], 75% retention is projected, resulting in 534 families, 1,068 children, and 887 parents at Wave 2;A repeated measures sample, comprising all observations from both waves. With a 75% family retention rate, the sample will include 1,246 (= 712 + 534) repeated family observations and 2,670 repeated child observations, and 2,216 repeated parent observations. The repeated measures sample will be the priority sample for testing study hypotheses.

Effective sample sizes are calculated for a two-level, mixed-effects model per Snijders [45] using an estimated within-family ICC = 0.30. Power is estimated for a standardized regression coefficient in a model with 5 covariates and alpha = 0.05. Effect sizes detectable at .80 power are listed in Table 1.

**Table 1 pone.0295007.t001:** Detectable effect sizes.

Direct, Moderation, and Mediation Effects (n = cross-sectional / panel / repeated)	Detectible Standardized Beta		
	Cross- sectional	Panel	Repeated Measures
**1. Family level predictors** (n = 712 / 534 / 1246; effective n = 1095 / 822 / 1917)	0.085	0.098	0.064
**2. Child level predictors** (n = 1424 / 1068 / 2492; effective n = 2034 / 1526 / 3560)	0.063	0.072	0.047

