**Simple Effects**			
**3. Family level predictors within risk and sex groups** (n = 356 / 267 / 623; effective n = 548 / 411 / 958)	0.120	0.139	0.091
**4. Child level predictors within risk and groups** (n = 712 / 534 / 1246; effective n = 1017 / 763 / 1780)	0.088	0.102	0.067

Power for tests 1 and 2 in the table apply to direct effects (**Aim 1** paths in Fig 1); mediation effects (products of path coefficients; **Aim 2** paths in Fig 1), and moderating effects (differences in slopes/interactions; **Aim 3** paths in Fig 1); Tests 3 and 4 represent simple slopes for associations within levels of the moderators family risk status and service member sex, which represent the lowest powered tests.

Some cite 0.10 as a “small” effect size for a partial correlation, which is comparable to a standardized beta coefficient [46]. Recent findings about effects of recent deployment (duration, trauma) effects on military youth outcomes gave standardized beta effect estimates in the range of 0.18 to 0.32, on average [44]. These reported effects were controlling for baseline levels in child outcomes and therefore represent effects on residual change, giving confidence that the study is adequately powered. Importantly, power will be further increased through the use of latent variables, which increase measure reliability [47], correlated mediators and outcomes in multivariate analyses [48], and including control variables that explain variance in mediators/outcomes (particularly true in panel analyses). However, power may decrease due to the unequal weighting effect [49].

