#### Analyses for aim 1: To assess direct relationships between the timing, frequency, duration and content of siblings’ early exposures to parental deployments and later youth adjustment

Maladjustment is hypothesized to be greater for children whose exposures began earlier (operationalized as child age at first deployment, including gestational age, coded from archival data), were more frequent (i.e., total number of deployments during the child’s lifetime) prolonged (i.e., total days deployed), ended more recently (i.e., days since end of most recent deployment), or who were exposed to deployments where parents’ experiences were more traumatic (i.e., total scores on self-report Combat Exposure items). These hypotheses will be tested using a SEM framework, where a series of path models will estimate the direct effects of deployment characteristics on each indicator of adjustment. Paths from the independent variables will be tested concurrently, thus establishing the unique association for each deployment risk factor. Interactions between different deployment components—frequency, duration, timing, and content—will also be examined to determine whether long-term effects of deployment are exacerbated or mitigated for various deployment combinations. Within-family comparisons will be conducted to determine whether these direct effects differ across siblings.

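### Table 1's detectable betas assume no overlap between predictors, so the .80 power does not carry over to the mutually adjusted deployment effects of Aim 1

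*Protocol article*

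**What the plan says.** All statements are in the protocol article.

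- **Sample size determination with statistical power calculation:** "Power is estimated for a standardized regression coefficient in a model with 5 covariates and alpha = 0.05". The next sentence reads "Effect sizes detectable at .80 power are listed in Table 1". The within-family ICC is 0.30. Row 1 (family-level predictors) has "effective n = 1095 / 822 / 1917" for the cross-sectional, panel and repeated-measures samples, and row 2 (child-level predictors) has "effective n = 2034 / 1526 / 3560". The column heading labels the entries as standardized betas. The repeated-measures sample is named as the priority sample.
- **Text under Table 1:** rows 1 and 2 are assigned to the direct effects of Aim 1. The reassurance begins "Some cite 0.10 as a “small” effect size for a partial correlation, which is comparable to a standardized beta coefficient". It then cites standardized betas of 0.18 to 0.32 from earlier work on deployment. Unequal weighting is the only factor named as lowering power.
- **Analyses for aim 1:** the exposures are age at first deployment, number of deployments, total days deployed, days since the last deployment ended, and combat exposure score. "Paths from the independent variables will be tested concurrently, thus establishing the unique association for each deployment risk factor". Interactions among the exposures are also to be examined.
- **Model building and estimation:** eight further controls are listed: parents' age, education, minority status and employment status, family type, family size, branch, and paygrade.

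**The concern.** The standard error of a standardized coefficient grows with sqrt(VIF), where VIF = 1/(1 − R²x) and R²x is the share of the exposure's variance explained by the other terms. A power figure for one coefficient needs a value for R²x, and the article gives none. If the table silently uses zero, it describes an exposure unrelated to everything else in the model.

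The Aim 1 exposures are not of that kind. Total days accumulate over the number of deployments. A child's current age is the sum of age at first deployment, the span of deployments, and the time since the last one ended. Current age is confined to 11 to 16, so these pieces trade off against each other.

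What is at stake is how a null result is read. If number of deployments and total days are each adjusted for the other, neither may reach significance although together they matter. A reader relying on Table 1 could take that as evidence of no effect.

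**Working it through.** **1. Reproduce Table 1.** Inputs: two-sided alpha 0.05, power .80, and the printed effective n. The formula is beta = (1.960 + 0.842)/sqrt(effective n) = 2.80/sqrt(effective n).

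- Row 1: 1095 gives 0.0847, 822 gives 0.0977 and 1917 gives 0.0640. Printed: 0.085, 0.098, 0.064.
- Row 2: 2034 gives 0.0621, 1526 gives 0.0717 and 3560 gives 0.0470. Printed: 0.063, 0.072, 0.047.
- Rows 3 and 4 agree in the same way. All 12 entries match to about 0.001.

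A one-sided alpha gives 0.075 for the first entry and does not fit. A noncentral F calculation with five other covariates gives 0.0844 against 0.0847, so the covariates cost almost nothing. The VIF implied by the 12 entries is 1.00 to 1.03. The table therefore has no allowance for overlap.

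**2. Power at the printed betas when VIF exceeds 1.** Power = Phi(2.80/sqrt(VIF) − 1.96).

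| VIF | R²x | Power |
|---|---|---|
| 1.25 | 0.20 | 71% |
| 1.5 | 0.33 | 63% |
| 2 | 0.50 | 51% |
| 2.5 | 0.60 | 43% |
| 4 | 0.75 | 29% |

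**3. Detectable beta at .80 power.** Beta = 2.80 × sqrt(VIF/effective n), with the effective n taken as printed.

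| Row and sample | VIF 1 | VIF 1.5 | VIF 2.5 | VIF 4 |
|---|---|---|---|---|
| Family, repeated (1917) | 0.064 | 0.078 | 0.101 | 0.128 |
| Family, cross-sectional (1095) | 0.085 | 0.104 | 0.134 | 0.169 |
| Family, panel (822) | 0.098 | 0.120 | 0.155 | 0.195 |
| Child, repeated (3560) | 0.047 | 0.058 | 0.074 | 0.094 |
| Child, cross-sectional (2034) | 0.062 | 0.076 | 0.098 | 0.124 |
| Child, panel (1526) | 0.072 | 0.088 | 0.113 | 0.143 |
| Family subgroup, panel (411) | 0.138 | 0.169 | 0.219 | 0.276 |

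**4. Which VIFs are plausible?** The documents give no correlations, so these are illustrations under assumptions. One simulation of the Aim 1 definitions assumed 0.5 to 3 extra deployments on average, each of 3 to 15 months. It gave these VIFs:

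- number of deployments: 4.0 to 4.6
- total days: 3.3 to 4.2
- time since the last deployment: 1.6 to 4.1
- age at first deployment: 1.1 to 1.6
- combat exposure: 1.3, but only because a correlation of 0.5 with total days was assumed

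A second simulation assumed one, two or three deployments in 50%, 30% and 20% of cases. It gave 4.8, 4.3, 4.2 and 2.6 for the first four. The two agree on number and total days, and differ on age at first deployment.

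**5. Margin against the cited effects.** The VIF at which the detectable beta reaches 0.18 is (0.18/beta at VIF 1)².

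- Family level, repeated measures: (0.18/0.0640)² = 7.9
- Family level, panel: (0.18/0.0977)² = 3.4
- Family level, panel subgroup: (0.18/0.1382)² = 1.7

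**The case against.** The best defence is that the article rests its adequacy claim on effects of 0.18 to 0.32, not on the betas in Table 1. In the priority sample a VIF of 4 still leaves detectable betas of 0.128 (family) and 0.094 (child). This stands, and it limits the point to the stated figures. A reader might infer that Aim 1 is underpowered outright; the documents do not support that.

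A reader might also infer that all five exposures are strongly interlocked. The definitions support this for number and total days, and in part for time since the last deployment. They do not show it for combat exposure, and the result for age at first deployment depends on the assumptions. A single-deployment illustration gives r about −0.80 between age at first deployment and time since, hence VIF 1/(1 − 0.64) = 2.8 and 39% power. There, however, number of deployments is constant, so it is not the Aim 1 model. Letting ages run to just under 17 changes it to r about −0.74, VIF 2.2 and 47%.

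The row matters too. Age at first deployment and deployments during the child's lifetime can differ between siblings, so row 2, or a value between rows 1 and 2, suits them better than row 1. Time since the last deployment is essentially a family-level quantity.

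The article lists gains from latent variables, multivariate analysis and outcome-explaining controls. These can offset modest overlap. With outcome R² of 0.3, power at 0.064 in the repeated sample returns to 80% if R²x is 0.3, but is only 66% at R²x 0.5 and 39% at 0.75.

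Read as partial correlations, the printed figures would already absorb the overlap. The table labels them standardized betas, however, and compares them with standardized betas. Finally, the article says emphasis will fall on effect sizes and confidence intervals, which would show collinearity as wide intervals. That softens the risk of misreading without correcting the table. A condensed article may also leave a joint test to the analysis plan. Its absence is not the defect; the mismatch between the power model and the stated Aim 1 model is.

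**Conclusion.** The point holds in a limited form. The arithmetic of Table 1 is correct for a predictor unrelated to the other model terms. Aim 1, to which the table is applied, estimates mutually adjusted effects of exposures that overlap partly by definition. For those exposures the .80 power at the printed betas is not met. The size of the shortfall depends on VIFs that the documents do not give, so the range above should be read as a sensitivity range; confidence in the mechanism is high and in the magnitude moderate. Detection of the cited 0.18 to 0.32 effects remains largely secure in the priority sample. It is less secure for family-level panel tests and least secure for family-level panel subgroups. The plan should be corrected, but the design is not shown to fail.

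**What to change.** 1. Restate Table 1 as 2.80 × sqrt(VIF/effective n) for all three samples. Take each exposure's VIF from the deployment records, or show VIF 1.5, 2.5 and 4. Use the row that matches the level at which each exposure varies.
2. Say that a partial correlation and a standardized beta are comparable only when predictor overlap and explained outcome variance are both small.
3. Report a joint test of the deployment exposures beside the concurrent model, so that a null adjusted effect of one exposure is not read as absence of a deployment effect.

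The cost is less favourable stated figures and one extra test per outcome. No new data are needed.

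### Table 1's repeated-measures column counts returning families as new ones, so its detectable effects for time-fixed family-level predictors are too small

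*Protocol article*

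**What the plan says.** All of this is in the protocol article, mainly in the section on sample size determination.

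- **Samples.** Wave 1 is "A baseline/cross-sectional analysis sample of 712 families and 1,424 children (2 per family), and 1,182 parents (1.66 per family"). For the panel, "75% retention is projected, resulting in 534 families, 1,068 children, and 887 parents at Wave 2". The repeated-measures sample pools all observations from both waves. The text gives it 1,246 family observations and "2,670 repeated child observations, and 2,216 repeated parent observations".
- **Priority.** "The repeated measures sample will be the priority sample for testing study hypotheses".
- **Method.** "Effective sample sizes are calculated for a two-level, mixed-effects model per Snijders [45] using an estimated within-family ICC = 0.30". The table's betas are those that can be detected with 80% power at a 5% alpha, after adjustment for five covariates. No correlation between the two waves is given.
- **Table 1, row 1 (family-level predictors).** "n = 712 / 534 / 1246; effective n = 1095 / 822 / 1917", with detectable betas 0.085 / 0.098 / 0.064.
- **Other rows, repeated-measures column.** Row 2 (child level): n 2492, effective n 3560, beta 0.047. Row 3 (family level within groups): effective n 958, beta 0.091. Row 4 (child level within groups): effective n 1780, beta 0.067.
- **Analysis.** The section on model building and estimation plans two kinds of model for change. One has three levels (time in child, child in family). The other has two levels (siblings in family) and adjusts for the Time 1 outcome.

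**The concern.** The 534 Wave 2 families are the Wave 1 families seen again 12 months later. A second reading of the same child adds less information about a fixed predictor than a reading from a new family. An effective n for both waves together therefore needs the correlation of a child's outcome with itself over the year, and with the sibling's outcome at the other wave. The power section uses one within-family ICC and a two-level model, while the three-level model planned for the pooled data has a time level.

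At stake is the column for the sample that is named as the priority for testing hypotheses. Several Aim 1 exposures, such as age at first deployment, are fixed or nearly fixed between waves, so this is the case that matters for them. Separately, the child and parent counts in the text do not follow from 75% retention.

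**Working it through.** **Inputs from the article:** 712 families at Wave 1, 534 at Wave 2 (so 712 − 534 = 178 seen once), two children per family, ICC 0.30, alpha 0.05 (taken as two-sided, which reproduces the table), power 0.80.

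**Inputs assumed, not in the article:** r, the same-child correlation across waves; c, the cross-sibling correlation across waves.

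**1. Reproducing Table 1.** With two children per family, effective n is children/(1 + ICC) for a family-level predictor and children/(1 − ICC) for a child-level predictor.

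- Family level: 1424/1.3 = 1095; 1068/1.3 = 822; 2492/1.3 = 1917.
- Child level: 1424/0.7 = 2034; 1068/0.7 = 1526; 2492/0.7 = 3560.
- Rows 3 and 4 are half of these.
- Detectable beta = (1.960 + 0.842)/√(effective n): 2.802/√1917 = 0.064; 2.802/√3560 = 0.047.

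All 12 effective n values reproduce, and all betas do to within about 0.001. The repeated-measures column is the sum of the two waves: 1095 + 822 = 1917, and 2034 + 1526 = 3560.

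**2. Family as the independent unit, predictor fixed over time.**

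- Family level: a two-wave family's mean of four readings has variance (1 + 0.30 + r + c)/4, and a one-wave family's mean of two has 1.30/2. Effective n = 534 × 4/(1 + 0.30 + r + c) + 178 × 2/1.30.
- Child level (differences between siblings): effective n = 534 × 4/(1 + r − 0.30 − c) + 178 × 2/0.70.
- Rows 3 and 4: half of these, as in Table 1.

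With r = c = 0 the first formula returns 2136/1.3 + 356/1.3 = 1917, so the printed figure is the case of no correlation across waves. The second returns 3560 whenever r = c.

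**3. Results with c = 0.30.**

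| | Stated | r = 0.30 | r = 0.5 | r = 0.7 |
|---|---|---|---|---|
| Row 1 effective n | 1917 | 1398 | 1291 | 1203 |
| Row 1 beta | 0.064 | 0.075 | 0.078 | 0.081 |
| Power at 0.064 | 80% | 67% | 63% | 60% |
| Row 3 beta | 0.091 | 0.106 | 0.110 | 0.114 |
| Row 2 effective n | 3560 | 3560 | 2882 | 2450 |
| Row 2 beta | 0.047 | 0.047 | 0.052 | 0.057 |
| Power at 0.047 | 80% | 80% | 71% | 64% |
| Row 4 beta | 0.067 | 0.066 | 0.074 | 0.080 |

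Example, row 1 at r = c = 0.30: 2136/1.9 + 356/1.3 = 1124 + 274 = 1398; 2.802/√1398 = 0.075. The 0.066 in row 4 is 2.802/√1780, the article's 0.067 to within rounding.

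In a more lenient case for row 1, r = 0.3 and c = 0.15, effective n is 1494, beta 0.073 and power at 0.064 about 70%.

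Row 3 reaches 0.10 when half the effective n is (2.802/0.10)² = 785. That requires 2136/(1.30 + r + c) = 1570 − 274 = 1296, so r + c ≈ 0.35. Any larger sum puts row 3 above 0.10.

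**4. Counts.** 1,424 + 1,068 = 2,492 child observations (text: 2,670). 1,182 + 887 = 2,069 parent observations (text: 2,216). Both printed counts imply 1,335 family observations (2,670/2; 2,216/1.66). That means 1,335 − 712 = 623 returning families, or 623/712 = 87.5% retention, against the 75% and 1,246 in the same sentence.

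**The case against.** Much of the other side stands.

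- **Child-level rows.** A reader might infer that all four rows share the fault. They do not fail when r = c: with every correlation at 0.30, row 2 returns exactly 3560. They are too optimistic only if a child resembles its own earlier self more than it resembles its sibling a year apart. That is likely, but the article gives neither correlation.
- **Predictors that change.** Days since the last deployment, mediators measured twice, and interactions with time do not follow these formulas. For effects on change within a child, positive correlation between waves can improve precision. The direction shown here is limited to predictors that do not change.
- **Model mismatch.** A two-level model is also planned, and it matches the panel column. The mismatch concerns only the pooled two-wave analysis.
- **Consequence.** A reader might infer that the study is underpowered or needs more families. The article judges adequacy against 0.10 for a small effect and earlier betas of 0.18 to 0.32. Corrected rows 1, 2 and 4 stay below 0.10, and row 3 stays well below 0.18. The 60% to 67% power is at 0.064, an output of the table and not an effect that the study expects.
- **Approximation.** The article itself names factors that may raise or lower power. These do not excuse counting one family as two.
- **Counts.** Table 1 uses 2,492 children and has no parent row, so the wrong counts affect no detectable effect.

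**Conclusion.** The point holds, within limits. The repeated-measures column treats the two waves as separate sets of families. For family-level predictors fixed between waves, the stated 0.064 and 0.091 are too small for any positive cross-wave correlation. Under the assumed c = 0.30 and r = 0.30 to 0.7 they become 0.075 to 0.081 and 0.106 to 0.114. The second wave then improves only modestly on the cross-sectional 0.085, and row 3 moves from below to above the article's own 0.10 benchmark. For child-level predictors fixed over time, 0.047 and 0.067 are right only if r = c; with c = 0.30 and r = 0.5 to 0.7 they become 0.052 to 0.057 and 0.074 to 0.080.

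The sizes rest on assumed r and c, on an ICC of 0.30 at both waves, and on families being retained or lost as a whole. The cross-sectional and panel columns are unaffected, and the adequacy statement for direct effects of 0.18 to 0.32 survives. The text counts are a minor separate error.

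**What to change.** 1. Recompute the repeated-measures column of Table 1 with the two formulas in the working, halved for rows 3 and 4. State r and c, say where they come from, and show a range.
2. Add that these figures apply to predictors that do not change between waves. Give time-varying predictors and interactions with time a separate calculation.
3. In the text, change 2,670 to 2,492 child observations and 2,216 to 2,069 parent observations. The 1,246 family observations are correct.

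The cost is one restated column, a sentence or two on assumptions, and two corrected counts. The column becomes less favourable. No extra families are needed, and neither the design nor the planned analyses change.

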### Sample

Data are being gathered from two siblings and up to two parents in 712 families where children will be aged 11 to 16 at the launch of data collection and living in the continental United States, at least half time with their military parent since the deployment. Children each will have experienced the same parental wartime deployment lasting at least 90 days, prior to age 6 for at least one child. A spouse or partner presently living with the military parent will also be invited to participate; an average of 1.66 parents per family is anticipated. Over 1 million service member parents have been deployed to Iraq and Afghanistan since 2001; 33.5% of their children are in the targeted age range [5, 42], yielding an estimated maximum pool of more than 200,000 families after accounting for families with only one child.

Families are not being excluded by divorce so long as the participating children have lived at least half time with the military parent. Families will be excluded if there is an active ongoing investigation for family violence; if any of the prospective participants has a significant cognitive impairment that would prevent comprehending or responding to questions; if the military parent is deployed during the study period; if only one adolescent is willing to participate; or if the military parent does not fit within a stratum with unfilled spaces.

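### Table 1 rows 2 and 4 use an effective sample size that fits only purely within-family predictors, so detectable effects are too favourable for exposures that siblings partly share

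*Protocol article*

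**What the plan says.** The section on sample size and power states: "Effective sample sizes are calculated for a two-level, mixed-effects model per Snijders [45] using an estimated within-family ICC = 0.30". It adds: "Power is estimated for a standardized regression coefficient in a model with 5 covariates and alpha = 0.05". Power is 0.80. The cross-sectional sample has 712 families and 1,424 children; for the panel, "75% retention is projected, resulting in 534 families, 1,068 children, and 887 parents at Wave 2".

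Table 1 row 2 (child-level predictors) reads "n = 1424 / 1068 / 2492; effective n = 2034 / 1526 / 3560", with detectable betas 0.063 / 0.072 / 0.047. Row 4 (child-level predictors within subgroups) reads "n = 712 / 534 / 1246; effective n = 1017 / 763 / 1780", with betas 0.088 / 0.102 / 0.067. Row 1 (family-level predictors) has effective n 1095 / 822 / 1917 and betas 0.085 / 0.098 / 0.064. Row 3 (family-level, within subgroups) has betas 0.120 / 0.139 / 0.091.

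The text below the table applies rows 1 and 2 to all three aims and rows 3 and 4 to simple slopes within moderator groups. It does not restrict rows 2 and 4 to any kind of child-level predictor.

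On eligibility, the Sample section says: "Children each will have experienced the same parental wartime deployment lasting at least 90 days". The analysis section for Aim 1 defines the exposures: child's age at first deployment, number of deployments in the child's lifetime, total days deployed, days since the last deployment ended, and the parent's combat exposure score.

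**The concern.** Dividing by (1 − ICC) credits the study with more information than it has observations. In a random-intercept model the gain arises because the sibling difference removes the shared family component. The full gain is available only when all of the predictor's variation lies between siblings of the same family.

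Deployment exposures are not generally of that kind. They come from a parent's deployments, and the siblings have at least one deployment in common. Part of their variation therefore lies between families, where the ICC costs information. The stated betas for the main predictors are then smaller than the design can detect at 80% power. Table 1 also gives no figure for a within-family slope expressed in units of the raw exposure SD, although comparing siblings is presented as a main contribution of the study.

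**Working it through.** **Inputs.** From the power section: ICC = 0.30, alpha 0.05 (sidedness is not stated; two-sided reproduces the table), power 0.80, two children per family, families 712 / 534 / 1246 for the three samples. Row 4 has half the families: 356 / 267 / 623. The sibling correlation r of the exposure is not given in the documents, so it is an assumption here and is shown over a range.

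**Reproducing the table.**
- Row 2: 1424/0.7 = 2034.3; 1068/0.7 = 1525.7; 2492/0.7 = 3560.0.
- Row 4: 712/0.7 = 1017.1; 534/0.7 = 762.9; 1246/0.7 = 1780.0.
- Row 1: 1424/1.3 = 1095.4; 1068/1.3 = 821.5; 2492/1.3 = 1916.9.
- Detectable beta = (1.960 + 0.842)/√(effective n) = 2.8016/√(effective n). Row 2 gives 0.0621 / 0.0717 / 0.0470 and row 4 gives 0.0879 / 0.1014 / 0.0664, all within 0.001 of the stated values. A noncentral F calculation agrees within 0.001.

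The arithmetic is sound. The question is the assumption behind it.

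**General formula for sibling pairs.** In a random-intercept model, the generalised least squares information on a pooled slope corresponds to

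effective n = families × [(1 − r)/(1 − ICC) + (1 + r)/(1 + ICC)].

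At r = −1 this is 712 × 2/0.7 = 2034, which is row 2. At r = 1 it is 712 × 2/1.3 = 1095, which is row 1. The two rows are the two ends of one formula.

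**Row 2, cross-sectional, over r.** Example at r = 0.5: 712 × (0.5/0.7 + 1.5/1.3) = 712 × 1.8681 = 1330. Power at the stated beta is Φ(0.063 × √1330 − 1.96) = Φ(0.338) = 63%.

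| r (assumed) | effective n | detectable beta | power at 0.063 |
|---|---|---|---|
| −1 (as stated) | 2034 | 0.062 | 81% |
| 0 | 1565 | 0.071 | 70% |
| 0.5 | 1330 | 0.077 | 63% |
| 0.8 | 1189 | 0.081 | 58% |
| 1 | 1095 | 0.085 | 55% |

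A simulation with 712 families (4,000 runs per value) gave 80%, 71%, 63% and 59% at r of about −1, 0, 0.5 and 0.8.

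**All three samples at r = 0.5.**
- Row 2: 1330 / 998 / 2328, betas 0.077 / 0.089 / 0.058.
- Row 4: 665 / 499 / 1164, betas 0.109 / 0.125 / 0.082.
- Power at the stated betas is about 62% to 63% in both rows.

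The repeated-measures figures here make no allowance for correlation between a child's two waves.

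**Within-family slope on the raw exposure SD.** Only the first term of the formula remains: effective n = families × (1 − r)/(1 − ICC). Cross-sectionally, r = 0.5 gives 712 × 0.5/0.7 = 509 (beta 0.124), and r = 0.8 gives 712 × 0.2/0.7 = 203 (beta 0.196).

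**The case against.** The defence of the table has real substance.

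- A reader might infer that an effective n above the number of observations is an error in itself. It is not: it occurs whenever r is below the ICC. Row 2 is exactly right for a family-mean-centred predictor, or for older versus younger sibling, scaled by its within-family SD. The section on model building does plan to estimate within- and between-family variability. What is missing is any statement that rows 2 and 4 are confined to such predictors.
- Rows 1 and 2 already bracket the answer for pooled slopes. That stands, but the table does not say that a mixed exposure falls between them.
- Some exposures belong under row 1. The combat score is the parent's own, and recency is essentially common to siblings who shared a deployment. That also stands, and it argues for assigning each exposure to a row.
- Sharing one deployment does not fix r for age at first deployment, because siblings of different ages meet the same deployment at different ages. A reader might conclude that the true effective n is known to lie close to row 1. The documents do not support this, since they give no r for any exposure.
- A reader might take the repeated-measures loss to be much larger, because 3560 also treats the two waves as independent. That is a separate issue, which the sibling formula does not contain, and it is not counted here.
- A reader might infer that the sibling contrast is far weaker than every row shown. At r = 0.5 it is not: 0.124 compares with 0.120 (cross-sectional) and 0.139 (panel) in row 3. It becomes so at r = 0.8.

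**Conclusion.** The point holds, with moderate severity. Rows 2 and 4 rest on an unstated condition, r = −1, that deployment exposures in general do not meet. For any r above −1 the stated effective n is too large and the stated beta too small. If r is between 0 and 0.8, the row 2 cross-sectional beta is 0.071 to 0.081 instead of 0.063, and power at 0.063 is about 70% down to 58%. These values depend on the assumed r and on the article's own ICC of 0.30.

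It would be tempting to conclude that the study is underpowered. The documents do not support that for pooled slopes. Corrected row 2 betas never exceed those of row 1, corrected row 4 betas never exceed those of row 3, and all stay below the 0.18 to 0.32 that the article cites in support of adequacy. The margin is thinner only for within-family slopes on the raw exposure scale: at r = 0.8 the detectable beta of 0.196 exceeds the lower end of that range.

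**What to change.** 1. Recompute rows 2 and 4 with families × [(1 − r)/(1 − ICC) + (1 + r)/(1 + ICC)], using the sibling correlation of each exposure. It can be calculated from the deployment records and birthdates that the study draws on. Until then, show a range of r.
2. If the present figures are kept, label them as applying only to purely within-family predictors scaled by their within-family SD.
3. Place exposures that siblings essentially share, such as the parent's combat score, under row 1 (row 3 within subgroups).
4. Add a row for the within-family slope on the raw exposure SD, families × (1 − r)/(1 − ICC), and name the scale.

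The cost is a table edit, a short note and one calculation on administrative data. Sample size, data collection and planned analyses do not change. The stated detectable effects become less favourable.
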